# Feasibility study of the effects of art as a creative engagement intervention during stroke rehabilitation on improvement of psychosocial outcomes: study protocol for a single blind randomized controlled trial: the ACES study

**DOI:** 10.1186/1745-6215-15-380

**Published:** 2014-09-28

**Keywords:** Stroke, Art, Mood, Self-esteem, Health status

## Abstract

**Background:**

Benefits of art participation after stroke are becoming increasingly recognized. Qualitative studies suggest that participation in visual arts creative engagement interventions (CEIs) during rehabilitation after stroke may improve mood, self-esteem, hope and some aspects of physical recovery. This study examines the feasibility of undertaking a randomized controlled trial of a CEI delivered by artists within in-patient stroke rehabilitation to test effectiveness.

**Methods/Design:**

This trial is a two arm, single-blind, randomized controlled feasibility trial within in-patient stroke rehabilitation. We will recruit 80 patients receiving stroke rehabilitation in two stroke units in a health board area of Scotland (40 patients in each arm). Intervention arm participants will receive a visual-arts based CEI facilitated by experienced artists. Artists will follow an intervention protocol with specific components that enable participants to set, achieve and review artistic goals. Participants will receive up to eight intervention sessions, four within a group and four one-to-one with the artist. Control group participants will receive usual care only.

Data collection will occur at baseline, post-intervention and three-month follow-up. Stroke-related health status is the primary outcome; mood, self-esteem, self-efficacy, perceived recovery control and hope are secondary outcomes. Semi-structured interviews will be conducted with purposively selected patients, artists and healthcare staff to elicit views and experiences of the intervention and feasibility and acceptability of trial processes. Recruitment rates, retention rates and patient preference for art participation will also be collected. Data will indicate, with confidence intervals, the proportion of patients choosing or refusing participation in the CEI and will allow calculation of recruitment rates for a future definitive trial. Summary data will indicate potential variability, magnitude and direction of difference between groups. Findings will inform sample size calculations for a definitive trial. Thematic analysis of qualitative data will be managed using the Framework Approach. Framework is an analytical approach for qualitative data, commonly used in policy and medical research.

**Discussion:**

If shown to demonstrate effects, this intervention has the potential to address aspects of stroke recovery previously. Not routinely addressed in rehabilitation.

**Trial registration:**

Registered with Clinical Trials.Gov: NCT02085226 on 6th March 2014.

**Electronic supplementary material:**

The online version of this article (doi:10.1186/1745-6215-15-380) contains supplementary material, which is available to authorized users.

## Background

More than 150,000 people in the United Kingdom experience a new stroke per year [1]. Stroke is the main cause of complex adult disability [2], with more than 300,000 people living with its effects at any time. As many as 85% of stroke survivors experience hemiplegia, which leads to impaired motor control on the affected side of the body. In addition, survivors often experience cognitive and communication impairments that, combined with physical impairments, lead them to experience loss of independence in activities of daily living and restricted return to participation in life roles [1].

Consequently, many survivors experience negative psychosocial consequences of the stroke that further compound its effects. Depression and anxiety are common, affecting 28 to 33% of stroke survivors at any time [3]. These mood disorders are associated with lower levels of independence in activities of daily living [4–6]. Additionally, survivors with low self-esteem experience lower functional status and higher levels of depression than those with more positive views of self [7, 8]. Unsurprisingly, many survivors also report low confidence or self-efficacy in everyday life that is also linked to depression, and loss of independence in activities of daily living [9]. The inherent consequences of these psychosocial effects of stroke and their impact on wider recovery mean that quality of life after stroke is significantly reduced [10]. It is therefore imperative to address these psychosocial consequences, both for the patient and family members

Post-stroke in-patient rehabilitation, typically involving professionals such as physiotherapists, occupational therapists and speech and language therapists, aims to restore physical functioning and communication to enable survivors to return home. However, despite advances that have improved survival rates and recovery of physical independence [11], rehabilitation remains a task-orientated process, focusing on practical daily living. Additionally, rehabilitation tends to adopt a deficit reduction model that focuses on what survivors cannot do, rather than on what they can do [12]. The need to address the psychosocial consequences of stroke are, however, being increasingly recognized and several policy documents now view their management as extremely important, emphasizing the need to improve life after stroke [13–15]. The potential role of adjunct rehabilitation interventions to address psychosocial problems and improve post-stroke quality of life should therefore be explored.

There is growing and convincing evidence that engaging in creative arts activities can promote improvements in perceived physical and mental health, social functioning and wellbeing in long-term conditions. Creative arts programs positively contribute to the wellbeing of people with mental health problems [16–19], cancer [20], dementia [21], brain injury [22] and diabetes [23]. Furthermore, the importance of arts in health is reflected in a recent United Kingdom Department of Health report that emphasized the importance of patient engagement in creative arts for the delivery of better health and wellbeing, and for improved healthcare experiences [24].

For stroke survivors, arts programs have the potential within rehabilitation to address some of the psychosocial consequences of stroke and to improve post-stroke quality of life [25]. A number of programs have been implemented to provide opportunities for survivors to participate in the creation of artwork using a range of visual arts media. Professional artists lead the programs [25, 26] and the focus of the activities is on the positive influence of engagement and participation in the art form. Activities are purely creative and do not involve specific assessment and treatment of psychological status normally undertaken by art therapists. The growing interest in visual arts creative engagement interventions (CEI) as adjunct interventions to traditional healthcare is increasingly reflected in stroke literature. Recent qualitative studies have illustrated the perceived positive impact of creative interventions on achievement of rehabilitation goals and outcomes, identity, mood and wellbeing during post-stroke rehabilitation [26, 27].

Visual art interventions may achieve these effects by enhancing control over recovery through development of confidence, leading to enhanced self-esteem [25, 26]. Theoretically, participation in a CEI may enable patients to make sense of their condition, in line with effects of expressive writing in acute and long-term conditions [28, 29]. Improved self-efficacy, perceived control and autonomy over the illness through creative activity are other ways in which the intervention might work to improve psychosocial outcomes after stroke [23].

However, whilst existing qualitative studies illustrate the perceived benefits and value of CEI to stroke survivors [25–27], the effects of the intervention on specific psychosocial outcomes after stroke has not yet been empirically tested. In health service settings that increasingly face financial challenges, empirical evidence from robust randomized controlled trials (RCT) that demonstrate the effectiveness of art on meaningful clinical outcomes is vital if CEI is to be incorporated as a routine adjunct intervention to rehabilitation.

Undertaking an RCT to evaluate the effects of a CEI on psychosocial outcomes is, however, challenging and a number of uncertainties need to be clarified before proceeding to a full-scale phase III trial. Firstly, the feasibility of undertaking a trial of a non-traditional intervention in a rehabilitation setting needs to be established. Art is an intervention in which preference for participation may strongly influence participant recruitment and attrition and therefore, before proceeding to a full trial, it is vital to identify the role of preference in recruitment and trial participation. Secondly, components of the intervention and their mechanisms of action need to be made explicit. Thirdly, the precise outcomes likely to be influenced by the intervention and corresponding appropriate measures that can be completed by stroke survivors need to be identified.

Selection of appropriate outcome measures is a particular challenge to researchers designing studies to measure the intervention effects of CEI. This is challenging given that the exact mechanisms by which art may influence psychosocial outcomes have not been fully established for stroke survivors. The present trial design is derived from an initial qualitative study that aimed to identify for the purposes of the trial, the components, mechanisms of action and perceived effects of an existing visual art CEI for stroke survivors receiving in-patient rehabilitation. Findings from the qualitative phase were used to design the feasibility trial intervention protocol and identify the outcomes to be evaluated to test the effects of the intervention. The purpose of the present study is to test trial processes to identify feasibility issues in running a CEI, to identify the primary outcome measure and to provide an assessment of effect size for power calculations for a full-scale Phase III trial. The purpose of this manuscript is to describe the trial design and protocol for a feasibility trial.

### Study aims

The aim of this study is to examine the feasibility of conducting an RCT to assess the potential effectiveness of a CEI to improve psychosocial health outcomes in patients receiving in-patient rehabilitation after stroke. To inform the development of a future Phase III trial, we will examine rates of recruitment of patients within in-patient rehabilitation wards to the trial. We will also examine the impact of preference for art on recruitment, retention and outcomes, and explore the acceptability and usefulness of the intervention from the perspective of patients and health professionals. A final aim is to estimate completion rates and effect sizes for relevant patient outcomes to inform the selection of a primary outcome measure and sample size calculations for a full-scale trial.

### Specific objectives

The objectives of this study are to examine the feasibility of intervention delivery in a trial context in two stroke rehabilitation units; to examine the feasibility of the trial processes, recruitment, retention and outcome assessment; and to provide estimates of the effect size of the intervention compared to usual care, in order to inform the development of a full-scale trial

## Methods/Design

We will conduct a single-blind randomized controlled feasibility trial [30]. People with a diagnosis of stroke consecutively admitted to two stroke rehabilitation units in northeast Scotland will be screened for trial inclusion within one week of their admission to rehabilitation. Those meeting inclusion criteria and agreeing to participate will be randomized to an intervention group who will receive the CEI for up to eight sessions with an artist, or a control group that will receive an art portfolio to view. Outcomes will be examined at the end of the intervention and at three-month follow-up.

The rehabilitation units provide rehabilitation services to stroke survivors following discharge from acute stroke units. Admission to a rehabilitation unit typically occurs less than two weeks after stroke onset, and the average rehabilitation stay is 35 days. In the rehabilitation unit, survivors receive occupational therapy, physiotherapy and speech and language therapy as part of their usual care. The CEI will be additional to those therapies

### Ethical approval

This clinical trial will be conducted according to NHS research governance requirements. Patients who agree to allow the study team to access their clinical records will provide written informed consent. All patients will be made aware that they can withdraw from the research at any time. The East of Scotland Research Ethics Committee approved the study (reference number: 13/ES/0006). NHS Research and Development approval has been obtained from NHS Tayside (reference number: 2011GM01). NHS Tayside and the University of Dundee have provided a joint sponsorship agreement.

### Eligibility

#### Inclusion criteria

All stroke survivors admitted to rehabilitation will be eligible for inclusion if they are medically stable and referred for rehabilitation - evidenced by ability to participate in usual rehabilitation therapies; able to sit upright in a chair, supported or unsupported; and if the multidisciplinary team estimates that they will remain in the unit to receive three weeks or more rehabilitation.

#### Exclusion criteria

Stroke survivors will be excluded from the study if medical records report a diagnosis of transient ischaemic attack; if they have acute medical need, are unconscious or medically unwell as evidenced by inability to participate in usual rehabilitation activities; or if they are unable to provide informed consent.

### Recruitment

Nursing and rehabilitation staff will identify potentially eligible patients within one week of admission to either of the stroke unit research venues, or when patients are medically stable and able to participate. The nursing and rehabilitation staff will provide and explain information leaflets to patients about the study, with an invitation to participate. One of two study researchers will approach patients who indicate interest in participating. The study will be fully explained, questions will be answered and initial screening for participation based on communication and comprehension will be will be conducted. Written informed consent for participation will be obtained. Ability to provide informed consent will be guided but not limited by scores on the following measures:

#### The Montreal Cognitive Assessment

The Montreal Cognitive Assessment (MOCA) [31] is a 16-item screening assessment for mild cognitive impairment that was developed in response to the poor sensitivity of the Mini-Mental State Examination for detection of mild cognitive assessment. It is widely used in clinical practice and in studies involving stroke survivors and assesses performance attention, concentration, executive functions, memory, language, visual-constructional skills, conceptual thinking, calculations and orientation. It has good reliability in people with mild cognitive impairment, with an internal consistency of alpha = 0.83 and high test-retest reliability (r = 0.92) [31]. In the same study, high correlation with the Mini-Mental State Examination was also demonstrated (r = 0.87), indicating high criterion validity. The maximum score is 30 and scores of under 26 indicate cognitive impairment. We will use scores that are routinely collected by clinical healthcare staff to assess cognitive impairment.

#### The National Institutes of Health Stroke Scale

The National Institutes of Health Stroke Scale (NIHSS) [32] is a 15-item scale assessing neurological outcomes and degree of recovery after stroke. It assesses motor and sensory function, coordination, language, speech and hemi-inattention. It has established reliability and validity for use in clinical research. Its’ test-retest reliability is high, with mean kappa values between 0.66 and 0.77 [33]. The construct validity of the NIHSS has been demonstrated (r = 0.94) [33], and correlations with lesion volume have been demonstrated to be significant r = 0.37 (P < .001) [34]. The maximum score is 42 with higher scores reflecting greater severity of impairment. Scores of more than one on the communication or consciousness scales will be used as potential indicators of ability to provide informed consent. As well as communication, the scale provides a general assessment of stroke severity and will be used as a baseline characteristic.

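### The NIHSS consent guide contradicts the scale direction stated in the sentence before it: scores meaning worse impairment are called indicators of ability to consent

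*Protocol article*

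**What the plan says.** The Recruitment section introduces two measures with the words "Ability to provide informed consent will be guided but not limited by scores on the following measures". The measures are the Montreal Cognitive Assessment and the NIHSS.

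The NIHSS section gives the direction of the scale: "The maximum score is 42 with higher scores reflecting greater severity of impairment". The sentence that follows is the consent guide: "Scores of more than one on the communication or consciousness scales will be used as potential indicators of ability to provide informed consent".

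The Montreal Cognitive Assessment section gives its cut-off as a marker of impairment: "The maximum score is 30 and scores of under 26 indicate cognitive impairment". It does not tie that cut-off to consent.

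Under Exclusion criteria, patients are excluded "if they have acute medical need, are unconscious or medically unwell as evidenced by inability to participate in usual rehabilitation activities", and separately "or if they are unable to provide informed consent".

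**The concern.** On this scale a higher score is a worse score. A threshold of the form 'more than one' therefore picks out the more impaired patients, and the sentence attaches ability to consent to that group. Anyone applying the text literally would treat poorer communication or reduced consciousness as counting in favour of capacity.

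This matters because the sentence is not background. It supports an exclusion criterion, and it is the only place in the article where a numerical threshold is linked in words to consent. Communication impairment is also common ground in this population: the researchers screen on it before consent, and aphasia severity is listed among the baseline characteristics. The study exists to test trial processes for a later full-scale trial, so its screening rules are likely to be carried forward. A reader who reproduced eligibility from this article would copy a reversed guide.

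**Working it through.** No figure is involved, so there is nothing to compute. The check is one of logic, setting the stated direction of the scale against the stated threshold.

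1. **Direction.** The NIHSS section says that higher means more impaired, on a scale with a maximum of 42.
2. **Items.** The article does not give item scoring. I assume that the communication and consciousness items run the same way as the whole scale.
3. **Threshold.** Under that assumption, a score above one on such an item is a more impaired result than 0 or 1.
4. **Consequence attached to the threshold.** The text attaches potential ability to consent to scores above one.

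| Item score | Meaning by the stated scale direction | Sentence as written | Sentence with 'inability' |
|---|---|---|---|
| 0 or 1 | Less impaired | Not mentioned | Not mentioned |
| Above 1 | More impaired | Potential sign of ability | Potential sign of inability |

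Only the last column fits the scale direction in the row for scores above one. The article does not say what a score of 0 or 1 implies, so the idea that unimpaired patients are marked as unable to consent is an inference and not something the text states.

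5. **Companion measure.** The Montreal Cognitive Assessment cut-off is expressed in the direction of impairment. That suggests the NIHSS cut-off was meant to work the same way.
6. **Correction elsewhere.** The Eligibility, Recruitment, Trial procedures and Statistical analysis sections were read for a restatement of the NIHSS rule in the opposite direction. There is none.
7. **Weight of the rule.** The Recruitment section makes the scores a guide, and the sentence itself says only that they are potential indicators. Inability to consent excludes a patient whatever the NIHSS score, and unconscious patients are excluded under a separate clause.

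**The case against.** The strongest reply is that this is loose drafting and not a reversed rule. The sentence echoes the Recruitment section's phrase about ability to consent, and could be taken to mean only that such scores bear on the question of ability. The literal reading is so odd for an impairment scale that a trained researcher would be unlikely to follow it. Other safeguards also apply. A researcher explains the study, answers questions and screens the patient directly before written consent. Inclusion requires medical stability and the capacity to take part in usual therapies. The exclusion for inability to consent does not depend on the NIHSS. Finally, the Trial status section reports recruitment as finished, so a correction cannot change who was approached.

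Most of this stands, and it limits the consequences. It does not rescue the sentence. If the meaning were only that NIHSS scores inform the judgement, there would be no reason to single out scores above one. Naming one side of a threshold gives a direction, and that direction conflicts with the sentence before it. Nor is this a detail lost when the article condensed a longer protocol: the article states something wrongly and does not merely leave it out.

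A reader might go further and infer that the rule decided who was asked for consent, that patients lacking capacity were enrolled, or that the recruitment rate describes the wrong population. The documents support none of these. The score is not binding, the separate exclusions remain in force, and nothing shows that anyone was screened in the reversed direction.

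**Conclusion.** The contradiction is real and sits between two adjacent sentences. It is probably a slip of one word. Its reach is confined to the consent guide and to anyone reproducing eligibility from this article; the sample size and the analysis are untouched. The article gives no number of patients scoring above one on these items, so no practical size can be put on it. The conclusion rests on one assumption, that the items run in the same direction as the whole scale. That 'inability' was intended is likely but not certain, and the sponsor needs to confirm it. Because this is operative eligibility text supporting a consent safeguard, and costs almost nothing to put right, it should be corrected even though the likely effect is small.

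**What to change.** Reconcile the two sentences in the NIHSS section. Apparently 'ability' should read 'inability' or 'impaired ability', so that scores above one are potential indicators of inability to give informed consent. The rest of the sentence can stay.

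Then confirm that the screening form and the researcher training used the intended direction. With recruitment reported as finished, this is a check on what was done. It also ensures that a later trial does not inherit the reversed wording. No new capacity procedure is needed.

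The cost is one word in the text and a look at the screening and training documents. No numbers, analyses or trial procedures change.
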